### **3.7 COVID-19 Vaccines**

As of December 2020, the first of several vaccines developed specifically for COVID-19 have been approved by the European Medicines Agency (EMA). Like many other countries the government of the Netherlands is aiming to vaccinate the majority of its population by the end of 2021. Given the differences in effectiveness between manufactured vaccines, the uncertainties surrounding the duration of protection afforded by these vaccines, as well as the difficulty in vaccinating a large majority of the population in a timely manner, the (early) detection of COVID-19 in both unvaccinated and vaccinated individuals remains a crucial component to contain the pandemic in the future. It is expected that part of the sample will be vaccinated during follow-up. As we are interested in evaluating the experimental vs. the control condition in a real-world setting with both unvaccinated and vaccinated subjects, it is important that the V2 algorithms implemented in Period 2 are developed with vaccinated

subjects present in the Learning Phase. As such, individuals vaccinated prior to registering for the study will be eligible to enter the study, and vaccination during any period of the study will not affect ongoing participation of the subject within the study. At baseline and in the bi-weekly surveys over the course of their participation in the study, subjects will be asked whether they have received a COVID-19 vaccine (in the case of the surveys this will pertain to the preceding two weeks) and, if so, which one (see [Section 3.8](#)). Subjects that have been vaccinated during follow-up will be reminded that their participation in the study is just as vital as prior to vaccination, and will be asked to continue to follow the study procedures. They will continue to receive notifications from the Ava COVID-RED app depending on the condition that they are in and will be asked to keep getting tested when requested seeing as there is still uncertainty about the effectiveness of COVID-19 vaccinations in preventing minor or asymptomatic infection and/or further transmission of the SARS-CoV-2 virus.

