### 2.2 Secondary Objective(s):

1. To assess the health economic utilization of a wearable device and mobile application as measured by endpoints such as:
  - a. Number of tests for suspected SARS-CoV-2 infections
  - b. Number of hospitalizations
  - c. Number of ICU events
  - d. Number of days requiring breathing support (e.g. oxygen and/or ventilation)
2. To determine the incidence of SARS-CoV-2 infection during the study
3. Identify which features of the Ava bracelet and Daily Symptom Diary are the most predictive features
4. Assess the independent predictiveness of an algorithm derived from physiological data gathered by the Ava bracelet in addition to self-reported daily symptom data
5. To assess the time from algorithm indication to symptom onset in the subject
6. To assess the time from algorithm indication to testing of the subject
7. To determine how taking antipyretic medication affects physiological parameters among subjects using the Ava bracelet and Daily Symptom Diary
8. To determine how self-reported vaccinations cause changes in biophysical parameters from subject's given baseline measurements
9. To correlate the longitudinal symptoms reported by study subjects confirmed to have COVID-19 with changes over time in their physiological data
10. To characterise longitudinal symptoms and recovery dynamics reported by the study subjects to the presence or absence of lab-confirmed SARS-CoV-2 infection
11. To assess the adherence to daily symptom diary completion and Ava bracelet wearing and synchronising over time

12. To determine the time necessary to establish baseline physiological parameters per subject in the Learning Phase of the study
13. To determine if retrospective identification of the moment of potential SARS-CoV-2 infection is possible for subjects who are seropositive at the end of a period but were negative at baseline and did not receive an alert to get tested during the study
14. To determine the rate of breakthrough and asymptomatic COVID-19 infections among vaccinated individuals
15. To assess the influence of self-reported COVID-19 vaccinations on compliance to study procedures

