#### 8.1.2 Secondary study parameters/endpoints (if applicable)

Additional endpoints will be collected for analysis of the secondary objectives as listed in Section 2.

*Study condition compliance (collected with Ava COVID-RED app)*

- Duration of Ava bracelet use (amount of days between first day of synchronised data and last day of synchronised data)
- Duration of daily symptom diary use (amount of days between first day completed symptom data and last day completed symptom data)
- Compliance rate: percentage of days (as compared to duration of use) that Ava bracelet was worn and synchronised.
- Compliance rate: percentage of days (as compared to duration of use) that symptoms were entered into the Daily Symptom Diary of the Ava COVID-RED app

*Longitudinal characteristics of study population (collected with Ava COVID-RED app)*

- Number/percentage of non-antipyretic and antipyretic medication days
- Number and type of vaccination events
- Number/percentage of days with alcohol consumption
- Number/percentage of days with recreational drug usage
- Number/percentage of days with period (menstruating women only)
- Number of pregnancy events (menstruating women only)

*Overall incidence of SARS-CoV-2 (collected through self-reporting of PCR/antigen test results in the Ava COVID-RED app and serology results)*

- SARS-CoV-2 cumulative incidence by condition and by stratum

*Healthcare Resource Utilization (collected throughout the study through bi-weekly surveys in COVID-RED web portal, structured interviews, and Ava COVID-RED app)*

- Number of COVID-related contacts from subjects to their general practitioner (GP)
- Number and duration of COVID-related hospitalization episodes
- Number and duration of COVID-related intensive care unit (ICU) episodes
- Number and duration of COVID-related supported breathing intervention
- Number and percentage of subjects with each reported medication used during hospitalization (WHO Drug Dictionary [WHO-DD])

*COVID-19 Testing (collected throughout the study through bi-weekly surveys in COVID-RED web portal and Ava COVID-RED app):*

- Number of tests conducted by GGD
- Number of provided PCR kits used
- Number of tests conducted due to red-light indicator of Ava COVID-RED app
- Time between first recommendation for testing and contact with GGD
- Time between first recommendation for testing and contact with study team for PCR sample kit

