- Time between first recommendation for testing and GGD SARS-CoV-2 test (stratified for antigen or PCR test if applicable)
- Time between first recommendation for testing and provided PCR SARS-CoV-2 test
- Time between first recommendation for testing and GGD SARS-CoV-2 test result (stratified for antigen or PCR test if applicable)

- Time between first recommendation for testing and Central laboratory SARS-CoV-2 test result

*COVID-19 Vaccination (collected during baseline and throughout the study through bi-weekly surveys in COVID-RED web portal)*

- Number of subjects who received a first and second (where relevant) dose of a COVID-19 vaccination stratified by manufacturer of the vaccine
- Time between first and second (where relevant) dose of the vaccine

*Behaviour (collected throughout the study through bi-weekly surveys in COVID-RED web portal):*

- Number of behavioural changes
- Behavioural changes made and reasons
- Number of behavioural changes (partly) due to the app or wearable
- Behavioural changes (partly) due to the app or wearable and reasons

*Daily Symptom Diary data (collected daily with Ava COVID-RED app)*

- Number and duration of each contiguous reported symptom:
  - Head:
    - Confusion
    - Difficulty concentrating
    - Dizziness
    - Fever
    - Headache
  - Nose and mouth:
    - Bluish lips or face
    - Loss of smell
    - Loss of taste
    - Nasal congestion or runny nose
  - Throat and sternum:
    - Nausea
    - Sore throat
    - Vomiting
  - Chest:
    - Chest tightness, pain or pressure
    - Dry cough

- Shortness of breath or difficulty breathing
- Lower back:
  - Chills or excessive sweating
  - Fatigue
  - Muscle or body aches
  - Skin impurities
- Abdomen:
  - Abdominal pain or cramping
  - Diarrhoea
  - Stomach ache
- General malaise
- No symptoms to report
- Average oral temperature and number/percentage of daily deviations above 38 degrees (Celsius), when collected
- Time between first algorithm indication for testing and symptom onset

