#### **8.4.13 Logging any SARS-CoV-2 test results and vaccination in Ava COVID-RED app**

Subjects will be instructed to log results from a SARS-CoV-2 test, independent of where the test was obtained, directly into the Ava COVID-RED app via the Daily Symptom Diary. Results from the serum antibody testing will also be provided by the central laboratory directly to the primary investigators. If a test result is negative, the subject will continue with the study procedures as planned. If the test result is positive, the Ava COVID-RED app will continue in a COVID-positive mode during which the subject will remain in the study and will

still be asked to record symptom data and wear/sync the bracelet. However, the subject will not receive any further algorithm-based indicators; instead, they will see a constant message on their Ava COVID-RED app home screen suggesting they seek additional medical care if their symptoms worsen or fail to improve.

When subjects receive any kind of vaccine (including any COVID-19 vaccine), they can log this in the Ava COVID-RED app and provide details in an unstructured open-text response field following the prompt, “If you received a new vaccine within the prior 24 hours, please specify which one: [Vaccine]”. Subjects that have received a COVID-19 vaccine during follow-up will continue using the app as instructed at onboarding and should seek testing for SARS-CoV-2 when receiving the red light indicator as described above.

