#### **8.4.14 Periodic completion of survey**

Every two weeks, a survey will also be sent to obtain more specific details on the testing procedures, epidemiological, household, occupational data and behaviour of the subjects. These surveys will allow the subject to self-report details on if they took a SARS-CoV-2 virus test, where they took it, how long they waited after receiving an in-app indicator before contacting the GGD, the time until they took their own sample and sent it to the central laboratory (if applicable), the type of test they took, how long it took them to receive their test results, and the result itself. These characteristics will also give a sense of the risk for SARS-CoV-2 infection that a subject has and can reveal important epidemiological relations as detailed in the study objectives. In addition, specific structured questions will be asked to subjects if they received a COVID-19 vaccine, including which dose (i.e., first or second) and from which manufacturer.

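### The two-week look-back of the bi-weekly vaccination question leaves a gap in the structured record whenever a survey is skipped, and no catch-up question is described

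*Protocol*

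**What the plan says.** Protocol Section 3.7 asks about COVID-19 vaccination at baseline and in the bi-weekly surveys, and restricts each survey's question: "in the case of the surveys this will pertain to the preceding two weeks". Section 8.4.14 gives the frequency ("Every two weeks, a survey will also be sent to obtain more specific details") and says that the vaccination questions are structured, "including which dose (i.e., first or second) and from which manufacturer".

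Section 3.8 (item 4) and the COVID-19 vaccination block of Section 8.1.2 name the surveys as the source, the latter together with baseline. The endpoints listed there are "Number of subjects who received a first and second (where relevant) dose of a COVID-19 vaccination stratified by manufacturer of the vaccine" and the time between the two doses.

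There is a second route. Section 8.4.13 says: "When subjects receive any kind of vaccine (including any COVID-19 vaccine), they can log this in the Ava COVID-RED app". The app prompt refers to the prior 24 hours and is answered in open text. Section 8.1.2 also lists "Number and type of vaccination events" among the app-collected characteristics. The protocol does not say how app and survey records are combined.

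Vaccination status is used in several places. Section 10 makes vaccinated subjects a key subset for the primary and secondary endpoints and allows sensitivity analyses that truncate data after vaccination. Objectives 8 and 14 in Section 2.2 depend on it, as does objective 15: "To assess the influence of self-reported COVID-19 vaccinations on compliance to study procedures".

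**The concern.** A two-week look-back asked every two weeks covers each day once. If one survey is not completed, nothing in the described survey asks about those days again. The study is fully remote and lasts up to nine months, so some surveys will be skipped.

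The main weakness lies in data collection, not analysis. A statistical analysis plan can define how vaccination status is derived, but it cannot supply a dose date that nobody asked for. The uses that need a date are the most exposed: the dose-interval endpoint, truncation after vaccination, and the before-and-after comparison in objective 8.

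Objective 15 carries a further risk. Its outcome is compliance with study procedures, while its exposure is known mainly through completion of another study procedure. If people who comply poorly also skip surveys, ascertainment of vaccination depends on the outcome under study. The app log is a weak safeguard here, because it relies on the same app engagement that the compliance measures record.

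**Working it through.** The protocol gives no survey-completion or app-logging rate, so there is no stated figure to reproduce. What follows is illustration on assumed rates.

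**Inputs**
- Survey interval: two weeks (Section 8.4.14). Look-back: two weeks (Section 3.7). Each day therefore falls in one window.
- Dose number is asked (Section 8.4.14), so a second-dose report shows that a first dose was given, though not when.
- Assumed: survey completion s = 0.90, 0.80 or 0.70, independent between windows, with the two doses in different windows.
- Assumed: probability a that the app log captures a dose, first 0, then 0.30.

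**Step 1: survey alone (a = 0)**

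| Quantity | Formula | s = 0.90 | s = 0.80 | s = 0.70 |
|---|---|---|---|---|
| Single dose in follow-up missed | 1 − s | 10% | 20% | 30% |
| Two-dose subject: no dose recorded | (1 − s)² | 1% | 4% | 9% |
| Two-dose subject: second dose missed | 1 − s | 10% | 20% | 30% |
| Two-dose subject: both doses recorded | s² | 81% | 64% | 49% |

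The last row matters for the dose interval. For the number of subjects with a second dose, one completed survey covering that dose is enough, so the third row applies.

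**Step 2: with some app logging (a = 0.30)**

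The miss probability for one dose becomes m = (1 − s)(1 − a).
- m = 0.10 × 0.70 = 7%, 0.20 × 0.70 = 14%, 0.30 × 0.70 = 21%.
- No dose of two recorded, m²: 0.5%, 2.0%, 4.4%.
- Both recorded, (1 − m)²: 0.93² = 86%, 0.86² = 74%, 0.79² = 62%.

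**Step 3: objective 15 with no true effect**

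Assume that half the subjects have diary compliance 0.9 and half 0.5. The true vaccination proportion v is the same in both halves, and anyone without a recorded dose is classed as unvaccinated.

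Worked case: v = 0.70, one dose, no app logging, survey completion 90% in high and 50% in low compliers.
- Recorded as vaccinated: 0.70 × 0.90 = 0.63 of high and 0.70 × 0.50 = 0.35 of low compliers.
- Mean compliance, recorded vaccinated: (0.9 × 0.63 + 0.5 × 0.35) / 0.98 = 0.757.
- Mean compliance, all others: (0.9 × 0.37 + 0.5 × 0.65) / 1.02 = 0.645.
- Spurious difference: 11.2 percentage points.

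The ranges below are for v from 0.50 to 0.85, one or two doses, and app logging of either none or 50% in high and 25% in low compliers:
- completion 95% versus 80%: 0.4 to 6.7 points;
- completion 90% versus 50%: 2.8 to 14.1 points;
- completion 80% in both: 0 (here app logging, where present, is also equal in both halves).

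The spurious difference thus needs two things: completion related to compliance, and unrecorded subjects treated as unvaccinated.

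**The case against.** The strongest reply is that the survey is not the only record, that no analysis rule mishandles the gap, and that the consequences are limited.

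- **The dose is not necessarily lost for good.** A reader might infer that it is. The app log and the dose-number question recover some doses, so the documents do not support that. What remains is that the log is optional, open text and limited to 24 hours, and that a second-dose report does not date the first. Section 8.4.9 lets symptoms be entered up to seven days late, but does not say this of vaccines.
- **No passage counts a subject with a skipped survey as unvaccinated.** Section 10 provides for investigating missing-data mechanisms, for imputation or robust methods, and for describing missing data. Section 10.5 keeps all subjects of a condition in the denominator of any percentage, but the vaccination endpoint is listed as a count. Rules for unknown status and for merging sources are normal analysis-plan content, so their absence here is no fault.
- **A 19/36/51% shortfall in the two-dose count does not follow.** It comes from applying 1 − s² to a count that needs only the second-dose report; the figure is 10/20/30%.
- **Objective 15 need not be biased.** A tempting extreme case is that vaccinated subjects stop everything at the dose and the whole drop in compliance disappears. It does not fit the protocol's measure. Section 8.1.2 defines compliance rates relative to duration of use, so stopping altogether shortens duration and need not change the rate.
- **The primary comparison does not use vaccination status.** It is between randomised conditions in Period 2, whose serology is anti-N. Truncation after vaccination is only something the sensitivity analyses may include.
- **A short look-back is a defensible way to limit recall error**, and the protocol summarises the question without showing the questionnaire.

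These points narrow the concern to a data-capture gap. They do not remove it, because no later analysis step can recover an unasked date.

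**Conclusion.** The concern holds as a data-capture weakness. As described, the structured vaccination record loses any dose given in a skipped window unless the app log or a later second-dose report recovers it.

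The effect on knowing who was ever vaccinated is small for two-dose courses and larger for single doses. The largest effect is on the dose interval and on anything else that needs both doses placed in time. All of these sizes rest on assumed, independent survey completion; app logging would reduce them, and completion that is correlated between windows would change them.

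For objective 15 the bias is a conditional risk whose size depends on rates and a coding rule that the protocol does not give. Nothing here touches the sample size, the stated power or the primary comparison between conditions. The change is still worth making, because it costs little and can only be made while data are being collected.

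**What to change.** Reword the survey item to ask for any COVID-19 vaccine dose received since the last completed survey, or not yet reported, with date, dose number and manufacturer for each. The date is needed because a longer look-back no longer places the dose within a two-week window. Repeat the item in the last survey of each period, so that a subject who returns after skipping surveys can still report earlier doses. When vaccination status is derived, combine these dates with the app log.

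The cost is one reworded question and one derivation step, with no extra contact. The downside is slightly longer recall for some dose dates. A subject who never completes another survey will still be unascertained from that point.

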### 3.8 Additional outcome measures

Additional outcome measures collected outside the Ava COVID-RED app will include:

1. Baseline demographic and risk factors (collected using an online form at subject registration)
2. Epidemiological and infection risk information (collected using bi-weekly online surveys)
3. Self-reported data on time to testing, testing procedures and the results (collected using bi-weekly online surveys)
4. Self-reported data on reception of COVID-19 vaccination (collected using bi-weekly online surveys)
5. Medical event reporting by subjects who have interactions with a general practitioner or a hospital related to SARS-CoV-2 infection, providing healthcare utilization measures during follow-up (collected using bi-weekly online surveys and followed-up by structured phone interviews)
6. Adverse device effects reporting by subjects (collected through the helpdesk [by phone or e-mail] and reminded in monthly online surveys and followed-up by structured phone interviews, if necessary)

See Figure 1 for an overview of the study design described above. See Figure 2 for an illustration of the planning and logistics of the trial as described above. Note that this is a schematic representation and may not fully reflect the exact conduct of the trial.

[figure not shown]

Figure 1: Study design of COVID-RED

[figure not shown]

Figure 2: Schematic illustration of the planning and procedures of the COVID-RED trial

## 4. STUDY POPULATION

### 4.1 Population (base)

A target of 20,000 subjects will be enrolled in this study. Subjects will initially be recruited from existing cohorts as well as via public campaigns. Members of existing cohorts will be contacted through email or mail to inform them about the COVID-RED study and to invite them to visit the COVID-RED web portal. For the public campaign, a public link will be available for any individual who wants to know more about the study and would like to participate. Subjects visit the COVID-RED web portal where it will be verified if the subject meets the criteria to join the study and information on participation in the study is provided. When the subject is interested to join the study the consent can be given in the portal. More details on the recruitment and consent process are included in section 8 and 11.2.

### 4.2 Inclusion criteria

In order to be eligible to participate in this study, a subject must meet all of the following criteria:

1. Resident of the Netherlands
2. At least 18 years old
3. Informed consent provided (electronic)
4. Willing to adhere to the study procedures described in this protocol
5. Must have a smartphone that runs at least Android 8.0 or iOS 13.0 operating systems and is active for the duration of the study (in the case of a change of mobile number, study team should be notified)
6. Be able to read, understand and write Dutch

### 4.3 Exclusion criteria

A potential subject who meets any of the following criteria will be excluded from participation in this study:

1. Previous positive SARS-CoV-2 test result (confirmed either through PCR/antigen or antibody tests) (self-reported)
2. Current suspected (e.g. waiting for test result) coronavirus infection or symptoms of a coronavirus infection (self-reported)
3. Participating in any other COVID-19 clinical drug, vaccine, or medical device trial
4. Electronic implanted device (such as a pacemaker)
5. Pregnant at time of informed consent (self-reported)
6. Suffering from cholinergic urticaria (per the Ava bracelet's User Manual)

